### Sample size calculation

Based on an earlier meta-analysis, we estimated that the prevalence of confirmed active TB in close contacts of smear-positive cases would be 2.3% [28]. In the 2006 to 2007 National Prevalence Survey, approximately 50% of prevalent cases of TB did not report typical symptoms of the disease, suggesting that a substantial proportion of patients with prevalent disease are not diagnosed by routine passive case detection within the NTP. We estimate that screening with the combination of X-ray and symptoms will identify at least 75% of prevalent cases of active pulmonary TB. This represents an increase in case detection rate of 50% above that expected for passive case finding alone. To have 80% power to detect an effect of this size, we would need 3,313 contacts in each group (6,626 in total), without accounting for clustering [29].

The sample size was then adjusted for the clustered design of the study. The first level of clustering is at the level of the index case. We estimated that, on average, each index case would identify four close contacts who would consent to participate. Assuming that the intraclass correlation coefficient within households is 0.1, the design effect at this level will be 1.3. The second level of clustering is at the level of the districts. There were 152 cases of smear-positive pulmonary TB per district in 11 representative provinces in 2007. Assuming that 70% of smear-positive cases consent to participate in the study, there will be 106 index cases. If we assume an intraclass correlation coefficient for index cases within districts of 0.01, the design effect at this level will be 2.05. Hence, we anticipate an overall design effect of 2.67.

On this basis, we estimate that we need to recruit a total of 3,338 index cases and 8,829 contacts (of 2,207 index cases) in each group. Based on our assumptions, this would require us to approach all available patients diagnosed with smear-positive pulmonary TB in 21 districts in each group: 42 districts in total. To ensure that we have a conservative sample size calculation, we will recruit all eligible and consenting index cases and their contacts from 70 districts.

Specific quarterly recruitment targets will be set for each district, based upon the number of notified cases of smear-positive TB during the most recent year for which data were available, as a way of enabling districts to track their progress during the study.

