**Methods/Design:**

We will conduct a cluster randomized controlled trial of contact investigation within the national tuberculosis control program of Vietnam. Household contacts of patients with smear-positive pulmonary tuberculosis will be invited to attend district tuberculosis units for symptom screening, examination, and chest radiography on four occasions over a two-year period. The primary endpoint is clinically confirmed tuberculosis among contacts during the 24 months of follow-up, ascertained using capture-recapture analysis. Microbiologically proven tuberculosis and treatment completion rates among contacts diagnosed with tuberculosis will be secondary endpoints. The incremental cost-effectiveness ratio will be estimated. The study will have 80% power to detect a 50% increase in the primary endpoint in the active intervention arm compared with the control arm. The study will include 8,829 contacts in each of the active screening and control groups, within 70 districts in 8 provinces in Vietnam, in both rural and urban settings.

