### Rationale for the study

Recent prevalence surveys in countries with a persistently high prevalence of TB have found that a substantial proportion of disease is not detected by conventional passive case-finding strategies [6-8]. Strategies that increase the proportion of cases that are detected may interrupt ongoing transmission of *M. tuberculosis*, and reduce the prevalence of TB over time [9,10]. Case detection strategies that target high-risk populations and are integrated with national TB control programs [11] are most likely to be feasible and sustainable.

Contacts of patients with TB are known to have a high risk of developing the disease, particularly in the five years after exposure. A recent meta-analysis of studies including almost 900,000 contacts showed that 3.1% (95% confidence interval (CI), 2.2 to 4.4%) of contacts in studies from resource-limited settings and 1.4% (95% CI, 1.1 to 1.8%) of contacts in studies from high-income countries had co-prevalent TB [12]. In Vietnam, our previously reported cohort study of active case finding in tuberculosis (ACT1) found that among 545 household contacts, 0.7% had co-prevalent disease [13]. Consequently, contacts are a potentially high-yield population to screen for disease. Close contacts of TB patients are also identified relatively easily by TB control programs, which can build upon their existing therapeutic relationship with the TB patient. For these reasons, contact investigation, defined as the evaluation of contacts of known TB patients for disease or infection is potentially a worthwhile adjunct to an effective TB control program in resource-limited settings.

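### The 80% power rests on 2.3% as the control-arm yield, although the sample size section gives 2.3% as total prevalence and implies that passive detection finds about half of it

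*Protocol article*

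**What the plan says.** The Sample size calculation section builds its effect size in four steps.

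- Baseline: "we estimated that the prevalence of confirmed active TB in close contacts of smear-positive cases would be 2.3" (per cent).
- Missed cases: in the national survey, "approximately 50% of prevalent cases of TB did not report typical symptoms of the disease", from which the section infers that routine detection misses a substantial share.
- Screening yield: "screening with the combination of X-ray and symptoms will identify at least 75% of prevalent cases of active pulmonary TB".
- Effect: "This represents an increase in case detection rate of 50% above that expected for passive case finding alone".

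It then concludes that "we would need 3,313 contacts in each group (6,626 in total), without accounting for clustering". It multiplies by design effects of 1.3 (household) and 2.05 (district) to reach 8,829 contacts per group from 42 districts. Recruitment is widened to 70 districts so that the calculation is conservative.

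The abstract (Methods/Design) repeats the claim: "The study will have 80% power to detect a 50% increase in the primary endpoint in the active intervention arm". It gives 8,829 contacts per group within 70 districts.

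The primary endpoint (Primary and secondary endpoints and stratification) is clinically diagnosed TB over the two-year follow-up.

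**The concern.** The section describes 2.3% as the TB present among contacts and then describes each strategy by the share of it that is found. The control arm should therefore be expected to yield a fraction of 2.3%. The printed sample size behaves as if the control arm yields all of it.

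For a fixed relative risk and a rare outcome, the required number is roughly inversely proportional to the control proportion, so halving that proportion about doubles the requirement. The article is addressed to policy makers. If the trial finds no clear difference, they will read that result as coming from a study with 80% power for a 50% increase. The power figure should follow from the assumptions printed beside it.

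**Working it through.** **Inputs.** From the Sample size calculation section: prevalence 2.3%; screening finds at least 75% of prevalent cases; ratio to passive detection 1.5; power 80%; 4 contacts per index case; 106 index cases per district; ICC 0.1 (household) and 0.01 (district); 42 districts calculated, 70 planned. Assumed: two-sided 5% (alpha is not stated, but the match in step 1 supports it) and an equal split of 35 districts per group.

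**Formula.** n per group = [1.96·√(2p̄(1−p̄)) + 0.8416·√(p1(1−p1)+p2(1−p2))]² / (p2−p1)², where p̄ is the mean of p1 and p2.

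**1. Reproduce the plan's figure.** With p1 = 2.3% and p2 = 1.5 × 2.3% = 3.45%:

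n = (0.46318 + 0.19877)² / 0.0115² = 3,313.3, the printed 3,313.

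3,313 × 1.3 × 2.05 = 3,313 × 2.665 = 8,829, the printed target.

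Other readings of the text do not reproduce it:

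| Control vs active | n per group |
|---|---|
| 1.15% vs 1.725% | 6,726 |
| 1.533% vs 2.3% (2.3% as active yield) | about 5,020 |
| 1.725% vs 2.3% | 9,362 |
| 1.15% vs 2.3% | about 2,011 |

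**2. Yields implied by the paragraph.** Passive share = 75%/1.5 = 50%. Control = 0.50 × 2.3% = 1.15%; active = 0.75 × 2.3% = 1.725%.

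n = (0.32993 + 0.14163)² / 0.00575² = 6,725.8, so 6,726 per group before clustering. After clustering, 6,725.8 × 2.665 = about 17,924 per group.

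**3. Power at 1.15% vs 1.725%.** Power = Φ{[0.00575·√n_eff − 0.32993] / 0.16829}.

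- *8,829 per group, design effect 2.665 (42 districts).* n_eff = 8,829/2.665 = 3,313; power 50%.
- *8,829 per group over 70 districts, as in the abstract.* Index cases per district = 8,829/4/35 = 63. District design effect = 1 + 62 × 0.01 = 1.62; overall 1.3 × 1.62 = 2.11. n_eff = about 4,191; power 60%.
- *All 70 districts recruit as assumed.* 35 × 106 × 4 = 14,840 per group. n_eff = 14,840/2.665 = 5,568; power 72%.

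**4. What would give 80%.** With 14,840 per group and a control proportion of 1.15%, the detectable relative risk is about 1.56. For a relative risk of 1.5, the control proportion must be about 1.39%.

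**5. Range for 14,840 per group, relative risk 1.5.**

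| Control proportion | Origin | Power |
|---|---|---|
| 0.7% | earlier Vietnamese cohort, taken as control yield | 51% |
| 1.15% | half of 2.3% | 72% |
| 1.39% | break-even | 80% |
| 1.55% | half of the 3.1% meta-analysis figure in the Rationale section | 84% |
| 2.3% | as used in the plan | 95% |

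**The case against.** Four counter-arguments have force.

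**The trial is not the 42-district design.** A reader might infer from step 3 that the real power is about 50%. The documents do not support that: the figure joins 8,829 contacts to a design effect for 106 index cases per district, while the trial uses 70 districts. On the paragraph's fractions, the 70-district power is about 60% or 72%, depending on whether 8,829 or 14,840 per group is meant. Widening to 70 districts recovers much of the shortfall.

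**The endpoint is broader than prevalent confirmed disease.** It is clinically diagnosed TB over 24 months. Incident and unconfirmed cases could raise both arms above 1.15% and 1.725%, and a rise to about 1.39% in the control arm is enough in the fully recruited design. So it would go too far to call 1.15% vs 1.725% the correct rates, or to say that 3.45% means finding 150% of existing cases. The latter holds only for point prevalence. This stands as a limit on the finding, but does not rescue the text: the section calls 2.3% a prevalence, derives the effect from shares of prevalent cases, and never offers 2.3% as a 24-month control yield.

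**The passive share is inferred.** The text does not define it as one half; it gives about 50% without typical symptoms. One half follows from 75%/1.5. The 75% is also a minimum: at 78% detection (1.794%) against 1.15%, 14,840 per group gives about 80%. That is a larger effect than the stated 50% increase, however.

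**Local evidence points both ways.** The earlier Vietnamese cohort "found that among 545 household contacts, 0.7% had co-prevalent disease", which is lower, but it rests on about four cases (0.007 × 545 = 3.8) and counts co-prevalent disease only. The 3.1% (2.2 to 4.4%) for resource-limited settings in the same section is higher. Any range should show both directions.

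**Conclusion.** The inconsistency is real. The printed 3,313 and 8,829 require a control yield of 2.3%, while the same paragraph gives 2.3% as total prevalence and implies that passive detection finds about half. On those premises the unclustered requirement is 6,726 per group rather than 3,313, about twice as many. Power in the 70-district trial is then about 60% to 72%, so the 80% in the abstract and the sample size section does not follow from the stated inputs.

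This rests on a two-sided 5% test, the plan's own ICCs and recruitment assumptions, an equal split of districts, and the inferred 50% passive share. It does not establish the trial's true power, which depends on a 24-month control proportion that the article does not state. If 2.3% can be justified as that proportion, the fully recruited design has about 95% power.

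**What to change.** 1. In the Sample size calculation section, state the expected 24-month proportion with clinically diagnosed TB in each arm and its basis. Separate prevalent cases found by each strategy from any allowance for incident and unconfirmed cases.
2. Recompute from those proportions. Restate power and the detectable relative risk for the 70-district design, in that section and in the abstract, and say whether 8,829 or about 14,840 contacts per group is meant. If the control proportion is 1.15% and recruitment is as assumed, the values are about 72% and 1.56; 80% at a relative risk of 1.5 needs about 1.39%.
3. Add a power table over control proportions that covers both the low and the high figures in the document, for example 0.7% to 2.3%.

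No additional enrolment and no change of endpoint or analysis is asked for. The cost is rewording one section and the abstract, and a less favourable stated power unless a higher control proportion is justified.

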### Analysis of effectiveness

The effectiveness of the active case finding in contacts will be assessed by comparing the case detection rate between contacts of index cases in the active intervention and control districts. There are two levels of clustering in the selection of contacts: the district in which the contact lives and the index case with whom he or she was in contact. To account for these two levels of clustering, we will undertake a mixed model analysis in which districts and index cases within districts are random effects and active versus control status is the fixed effect. The measure of effect will be relative risk, estimated using a log link and binomial error distribution. In this primary analysis, there will be no adjustment for baseline characteristics. However, in a subsidiary analysis we will examine the impact of baseline characteristics of the districts, including geographical characteristics and baseline case notification rate, and individuals, including age and sex, on the risk of disease by testing these characteristics as potential effect modifiers.

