### Selection of study districts

The study will be conducted in 70 districts within eight provinces. These provinces have been selected to include four provinces in the south (Ho Chi Minh City, Can Tho City, and the rural provinces of An Giang and Tien Giang), where the prevalence of TB is highest, two provinces from the central area (Da Nang Province and the rural province of Binh Dinh), and two provinces from the north (Hanoi City and the semi-rural province of Vinh Phuc). This geographic and urban-rural stratification is important because the incidence of TB increases from the north to the south within Vietnam [7]. There are also substantial differences in lifestyle and infrastructure between rural and urban areas. Hence, the selection of this diverse range of sites will increase the generalizability of the study findings.

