### Randomization

Among the 97 districts within these eight provinces, 70 have been randomly selected for participation in the trial. These districts were selected with a probability proportional to their population size. The initially selected districts will enter a run-in period, prior to randomization, during which time they will be required to recruit two patients and six contacts and to demonstrate that they have the necessary resources to conduct the study. If districts fail or withdraw during this pre-randomization run-in period, they will be replaced by the next randomly selected district.

We will randomly allocate districts to the active intervention or control group using the minimization method with predefined randomization lists [27]. The minimization criterion will be province, to ensure balance of intervention and control districts within each province. District size will not be taken into account in the randomization process. Randomization will be performed by a person who is not otherwise engaged in the project, and is blinded to the identity of districts.

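### The primary model omits province, the only factor on which districts are balanced, so its standard error is somewhat too large and the test is conservative

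*Protocol article*

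**What the plan says.** The protocol article, Randomization, names a single allocation factor: "The minimization criterion will be province, to ensure balance of intervention and control districts within each province". Selection of study districts explains why geography matters: "the incidence of TB increases from the north to the south within Vietnam".

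Analysis of effectiveness then sets the primary model. It is a mixed model with a log link and binomial error in which "districts and index cases within districts are random effects and active versus control status is the fixed effect". It adds: "In this primary analysis, there will be no adjustment for baseline characteristics". Geographical characteristics, the district's baseline notification rate, age and sex appear only in a subsidiary analysis, which examines them "by testing these characteristics as potential effect modifiers".

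Sample size calculation uses the whole district intraclass correlation of 0.01, with no reduction for province or any covariate. It finds that 42 districts suffice and then enrols 70.

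**The concern.** When allocation is constrained to balance a prognostic factor, the arm difference no longer varies with that factor from one possible allocation to the next. A model without the factor does not know this. It places differences between provinces in the district random effect and counts them as noise in the arm comparison. The reported standard error then exceeds the true sampling variability, so intervals are too wide and the test rejects less often than its nominal level.

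At stake is precision, not validity. No bias arises and false positives are not inflated. The trial is meant to inform policy on contact investigation, however, and an interval wider than the design warrants makes an inconclusive reading more likely than it need be. Because the model is stated in the article and adjustment is ruled out there, this is not a detail left open for the analysis plan.

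**Working it through.** **Inputs from Sample size calculation.** Base rate 2.3%; relative increase 50%, so 2.3% against 3.45%; power 80%; household design effect 1 + (4 − 1) × 0.1 = 1.3; district design effect 1 + (106 − 1) × 0.01 = 2.05; 106 index cases per district and 4 contacts per index case. Alpha is not stated; 5% two-sided is assumed.

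**Reproducing the plan's figure.** The standard two-proportion formula without continuity correction gives 3,314 contacts per group, against 3,313 stated. Then 3,313 × 1.3 × 2.05 = 8,829, as stated. The whole district component is in this figure, so the planned 80% already belongs to an analysis without province.

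**Effect of omitting province.** Let f be the share of between-district variance that province explains. The documents do not give f, so a range is used, with near-perfect balance within province.

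- The unadjusted model's standard error carries a district design effect of 2.05.
- With province balanced, the estimate varies only as if it were 1 + 1.05 × (1 − f).
- Ratio of reported to true standard error: r = √[2.05 / (1 + 1.05 × (1 − f))].
- True alpha of the unadjusted test: 2 × [1 − Φ(1.96 × r)].

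Example at f = 0.50: r = √(2.05 / 1.525) = 1.16, and alpha = 2 × [1 − Φ(1.96 × 1.159)] = 2.3%.

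**Power at 70 districts.** There are 35 × 106 × 4 = 14,840 contacts per arm. Dividing by 1.3 × 2.05 = 2.665 gives about 5,568 effective contacts and power of 95.3% at f = 0. With f above 0, unadjusted power is Φ(r × Φ⁻¹(0.953)). Adjusted power uses 14,840 / [1.3 × (1 + 1.05 × (1 − f))] effective contacts.

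| f | SE ratio | True alpha, unadjusted | Power, unadjusted | Power, province fitted |
|---|---|---|---|---|
| 0.10 | 1.03 | 4.4% | 95.7% | 96.2% |
| 0.25 | 1.07 | 3.6% | 96.3% | 97.3% |
| 0.50 | 1.16 | 2.3% | 97.4% | 98.8% |
| 0.75 | 1.27 | 1.3% | 98.3% | 99.6% |

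With the 42 districts the plan calls sufficient (21 per arm), power for f = 0.25/0.50/0.75 is 82.0/83.9/86.2% unadjusted and 85.4/90.4/94.8% with province.

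**Simulation check.** District-level data were simulated 4,000 times per setting (70 districts, 8 provinces, balanced arms) and analysed by a t-test on log district rates. This is cruder than the planned model and has lower absolute power. For f = 0.25/0.50/0.75, type I error was 4.0/2.7/2.0% unadjusted and 4.8/4.7/4.8% with province. Power was 90.5/91.7/92.1% and 91.8/93.8/96.0%. The direction agrees; the power gain is somewhat larger because this test starts from lower power.

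**Lower event rates.** If the rates were 1.15% against 1.725% (the 2.3% multiplied by 50% and 75% detection), power at 70 districts would be 72.2% at f = 0. For f = 0.25/0.50/0.75 it would be 73.6/75.3/77.4% unadjusted and 77.9/84.0/90.1% with province. This scenario is an assumption and does not reproduce the plan's 3,313.

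**The case against.** The strongest reply is that the omission costs little. The sample size credits nothing to province, the plan enrols 70 districts where it needs 42, and on its own figures power is about 95% with or without province. The error is in the safe direction. Its size depends on f, which the protocol does not give: a north-to-south gradient in general incidence does not show how much of the district variation in detected disease among contacts lies between provinces. At f = 0.10 the excess in the standard error is 3%. All of this stands, and it limits the point to a modest gain in efficiency.

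Three stronger readings are tempting, and the documents support none of them.

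- **That the trial gives up power it had designed in.** The chain to 8,829 shows that the designed 80% is for an unadjusted comparison.
- **That leaving out the baseline notification rate also makes the standard error wrong.** It was not an allocation factor. Apart from any part it shares with province, its omission leaves a valid standard error for the unadjusted estimate.
- **That no adjusted effect will ever be produced.** A model testing effect modification would normally contain the main effects, and what is reported may be settled in an analysis plan that is not shown. It remains true that the stated primary result does not reflect the allocation.

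**Conclusion.** The point holds as an inexpensive improvement. The stated primary analysis is conservative, not invalid: it ignores the one factor that the allocation balances and that the protocol itself expects to be prognostic. For f between 0.25 and 0.75 the over-wide intervals are the main consequence, with a gain of only about 1 to 1.5 points in power. A larger gain, about 4 to 13 points, appears only if event rates are as low as 1.15% against 1.725%. These figures assume 5% two-sided alpha, near-perfect balance by province, and the plan's own cluster sizes and intraclass correlations. If province explains almost none of the district variance, the effect is negligible.

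**What to change.** Add province as a fixed effect with 8 levels to the primary log-binomial mixed model, keeping the random effects for district and index case. Amend the sentence on baseline adjustment to say that province is included because allocation was balanced on it. Specify this before outcomes are seen, since a later change would look data-driven. Keep the unadjusted model as a sensitivity analysis, and report effect-modifier tests separately from adjustment.

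The cost is 7 degrees of freedom out of 70 districts and no new data, as each district's province is known. With a log link and a common relative risk across provinces, the effect measure is unchanged. Adjustment for baseline notification rate, age and sex may be prespecified for further precision, but it is optional and corrects no error.
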